### Allocation

Allocation will be done by simple randomization using the random numbers generated from GraphPad Prism (version 9) for this study.

Arm A: The intervention for FBI.Arm B: The standard of care for neonates admitted into the unit born units of selected hospital.

Subjects will be allocated to two arms of this study in parallel (concurrent): FBI (Arm A) and standard of care (Arm B) based on the randomization process.

### Assignment of Interventions: Allocation

#### Sequence Generation

A random number will be generated using simple randomization from GraphPad Prism version 9 for consecutive patients being enrolled for this study.

#### Concealment Mechanism

This study will be an open label (masking not used).

#### Implementation

A record officer will be responsible for generating a random number and its allocation using GraphPad Prism version 9.

### Assignment of Interventions: Blinding

#### Who Will Be Blinded

This is an open label trial. The intervention and comparator will not be concealed. Both the investigator and the subject will be aware of what intervention they would receive.

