## Background and Rationale

Approximately 130 million babies are born annually, about 4 million of these newborns in low- and middle-income countries (LMICs) do not survive beyond the neonatal period (1). More worrisome is the increasing contribution of childhood mortality from the neonatal death. This narrative is not different in Nigeria where neonatal mortality represents one of the highest in the world, only behind India (2).

The reasons for this trend are multifactorial. They vary from ignorance, harsh healthcare workers altitude to caregivers/parents, poverty, the lack of access to good healthcare, the need for spiritual support at a very trying time, and discharged against medical advice (DAMA) (3–7). It is, therefore, important that those who get to a health service be treated holistically, providing physical, psychological, and spiritual support to enable them complete treatment until when discharge is recommended by the treating clinicians (3–5).

Discharged against medical advice occurs when an in-patient decides to leave the hospital before discharge is recommended by the treating clinicians or physicians. DAMA poses serious clinical, ethical, and legal challenges to the individual physician as well as to the hospital (1, 6–9). The DAMA prevalence has been shown to vary depending on geographical areas and the study population. The rate of DAMA compares inversely with the socioeconomic status: a relatively lower rate was observed at a hospital serving primarily middle- and upper-class populations, whereas a higher rate was observed at a hospital serving disadvantaged urban areas (9–13). The pediatric age group, and especially the newborns are at a greatest risk for DAMA in Nigeria from the published literature (9–11).

Discharged against medical advice has been shown to increase the risk of adverse outcomes ranging from medical complications requiring readmission to death (6, 8). Associated outcomes also include higher morbidity, increased mortality, longer hospital stays, and higher costs of treatment when readmitted (10, 11).

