### Outcomes

#### The Primary Outcome

The primary outcome of this study is the retention rate of sick newborns with the FBI in public tertiary hospitals in Nigeria compared with the standard of care.

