#### Procedure for Unblinding if Needed

This study will be an open label (masking not used).

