### Data Collection and Management

#### Plans for Assessment and Collection of Outcomes

Training will be held for the researcher prior to the commencement of the trial *via* online zoom meeting. The validated questionnaire, the trial protocol, religiosity, spirituality, and social scales would be tested. Experience on understanding the tools and the ease of administration of the tools would be assessed. The observation from the training will be incorporated into the study instruments to improve the data entry and address other observed limitations.

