### Oversight and Monitoring

#### Composition of the Coordinating Center and Trial Steering Committee

A trial steering committee consists of the Principal Investigator, two scientific enquirers, the public enquirer, and a biostatistician. They will meet frequently to provide an oversight function for the trial conduct over the two centers in the country.

Each center will have a hospital trial group headed by a consultant pediatrician, who will be saddled with running daily events in the hospital, providing organizational support, and reporting on a weekly basis to the steering committee.

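### The primary outcome turns on the clinician's discharge recommendation in a trial with no masking, and no one unaware of the arm classifies departures

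*Protocol article*

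**What the plan says.** Under The Primary Outcome, the protocol article states: "The primary outcome of this study is the retention rate of sick newborns with the FBI in public tertiary hospitals in Nigeria", compared with standard of care. That section does not say what makes a baby retained. The definition that separates the two outcomes is in Background and Rationale: "Discharged against medical advice occurs when an in-patient decides to leave the hospital before discharge is recommended by the treating clinicians or physicians".

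On masking, Who Will Be Blinded says: "Both the investigator and the subject will be aware of what intervention they would receive". Concealment Mechanism and Procedure for Unblinding if Needed each repeat that the study is open label and that masking is not used.

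On trial conduct, the section on the coordinating centre and steering committee says: "Each center will have a hospital trial group headed by a consultant pediatrician, who will be saddled with running daily events in the hospital".

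On outcome assessment, the article has its own section, Plans for Assessment and Collection of Outcomes. It covers training and the instruments: "The validated questionnaire, the trial protocol, religiosity, spirituality, and social scales would be tested". It names no one to classify departures. The data monitoring committee section gives information technology staff the task of entering data, not of judging outcomes.

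The primary comparison is a chi-squared or Fisher's exact test at p < 0.05 (Statistical Methods for Primary and Secondary Outcomes).

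**The concern.** When a family presses to leave, the clinician may hold to the view that the baby is not ready, and the departure is a DAMA. Or the clinician may agree to discharge, and the baby counts as retained. The family has behaved in the same way in both cases. The clinician's act and its timing decide the label.

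This matters little if the label is applied alike in both arms. Here nothing in the article keeps knowledge of the arm away from that decision or from its recording. The intervention also urges parents to stay until medical discharge, which is the event the outcome counts, so staff know what result it is meant to produce. If labels shift in one arm only, the trial can show a retention effect that is not there, or hide one that is. The planned test compares recorded proportions and cannot separate a change in labelling from a change in what families do.

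**Working it through.** **Inputs**

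- Total sample size 359 and DAMA prevalence 50%: Sample Size section.
- Two arms by simple randomization: Sampling Technique. The ratio is not stated; 1:1 is assumed, so n = 359/2 = 179.5 per arm.
- Test at p < 0.05: Statistical Methods. Sidedness is not stated; two-sided is assumed.
- Share m of one arm's DAMAs recorded as discharges: assumed, because the article gives nothing from which to estimate it.
- A second DAMA rate of 10%: assumed, to show how far the result depends on the 50%.

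**The plan's own figure.** The single-proportion formula at 50%, with 95% confidence and an assumed 5-point margin, gives 1.96² × 0.25 / 0.05² = 384.1, so 385 and not 359. A finite-population correction returns 359 only for a population of about 5,250 to 5,470, which the article does not state. That is a separate matter. Here 359 serves only as the number of babies to be analysed.

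**Step 1: who decides the label.** Put the definition beside the masking statements. The definition makes the treating clinician's recommendation the dividing line. The masking statements shield no role from the allocation. The outcome-assessment section adds no arm-unaware classifier. The route for differential labelling is therefore open.

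**Step 2: what it could do.** Let p be the true DAMA rate in both arms, so that there is no effect, and let q = p(1 − m) be the recorded rate in the arm with relabelling. With d = p − q and p̄ = (p + q)/2:

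- SE0 = √[2p̄(1 − p̄)/n]
- SE1 = √[(p(1 − p) + q(1 − q))/n]
- P(reject) = Φ[(d − 1.96·SE0)/SE1] + Φ[(−d − 1.96·SE0)/SE1]

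Example with p = 0.50 and m = 0.10: q = 0.45, d = 0.05, p̄ = 0.475. SE0 = √(2 × 0.475 × 0.525/179.5) = 0.0527, and SE1 = √((0.25 + 0.2475)/179.5) = 0.0526. P = Φ(−1.01) + Φ(−2.91) = 0.157.

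| True DAMA, both arms | Relabelled in one arm | Recorded DAMA | False-positive rate |
|---|---|---|---|
| 50% | 5% | 47.5% v 50% | 7.6% |
| 50% | 10% | 45% v 50% | 15.7% |
| 50% | 20% | 40% v 50% | 47.8% |
| 50% | 30% | 35% v 50% | 82.3% |
| 10% | 5% | 9.5% v 10% | 5.3% |
| 10% | 10% | 9% v 10% | 6.2% |
| 10% | 20% | 8% v 10% | 10.1% |
| 10% | 30% | 7% v 10% | 17.4% |

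The nominal rate is 5%. The calculation corresponds to the chi-squared test without continuity correction. The result is the same whichever arm is relabelled; only the direction of the apparent effect changes.

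**The case against.** Several points on the other side are fair.

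*The article does have a rule.* A reader might infer that nothing fixes how a departure is classified. That goes too far. The Background definition is an ordering rule: departure before the recommendation is DAMA. What the article lacks is a tie from that rule to dated events, and a classifier unaware of the arm.

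*Knowledge of the arm and motive are inferred.* A reader might take it as stated that treating clinicians know the arm and have a stake in the result. The blinding section names the investigator and the subject only. The committee section puts a consultant pediatrician at the head of each site's trial group, but does not say that this person decides discharges. With no masking for any role, ward staff probably know the arm. No stake in the result is documented.

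*The article is condensed.* A full protocol may hold classification rules or form fields. The point still stands on what is printed: the absence of masking is a stated choice, and the section devoted to outcome assessment offers no protection.

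*Open label is unavoidable for families.* This is true, and it is not the complaint. Families cannot be masked to prayer and counselling, but the person who classifies a departure can be.

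*The remedy has limits.* Counting every discharge agreed after a family request as DAMA would depart from the article's definition. A baby who was ready to go, and whose parents happened to ask first, would count as a failure. The counselling may also change how often families ask. That rule therefore belongs in a sensitivity analysis. A reader unaware of the arm also works from charts written by staff who may know it, so some bias would remain.

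**Conclusion.** The point holds as a risk built into the design. The primary outcome is partly a clinician's judgement, no role is masked, and the article provides no classification by anyone unaware of the arm. The planned test cannot separate differential labelling from a true effect on retention.

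The size of the bias is unknown. The rates of about 16% and 48% should not be read as this trial's expected false-positive rate. They rest on an assumed 10% or 20% relabelling confined to one arm, on 1:1 allocation, and on the 50% that the article enters in a single-proportion calculator, which is not a forecast for the control arm. At an assumed 10% DAMA the same shares give about 6% and 10%. The documents show that differential labelling is possible, not that it will occur. The change is worth making before outcomes are classified, because it is cheap and bears on the primary result.

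**What to change.** Keep the article's definition of DAMA as the primary rule and apply it to documented events:

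1. On the case form, record the date and time of the discharge recommendation, of any family request to leave and of the departure, and who initiated the departure.
2. Keep the allocation out of that record.
3. Have an existing team member without access to the allocation classify each departure from it. The steering-committee biostatistician would serve only if that person does not hold the allocation. Data-entry staff would serve only if they do not see it and the categories can be read from the recorded times without clinical judgement.
4. Add a sensitivity analysis that counts as DAMA any discharge agreed only after a family request.

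This alters how departures are recorded and counted, not when any baby is discharged.

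The cost is a paragraph in the outcome section, a few form fields and a little more work for existing staff. The remaining weakness should be stated: bias in what arm-aware staff write in the chart is reduced but not removed.

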#### Procedure for Unblinding if Needed

This study will be an open label (masking not used).

### Data Collection and Management

#### Plans for Assessment and Collection of Outcomes

Training will be held for the researcher prior to the commencement of the trial *via* online zoom meeting. The validated questionnaire, the trial protocol, religiosity, spirituality, and social scales would be tested. Experience on understanding the tools and the ease of administration of the tools would be assessed. The observation from the training will be incorporated into the study instruments to improve the data entry and address other observed limitations.

#### Plans to Promote Participant Retention and Complete Follow-Up

This study's outcome would be measured at a single time point, with no follow up.

### Data Management

The data obtained from this study will be entered into a password and encrypted institutional Red Cap database. Only specific individuals from the collaborating centers will be given access to the database. The data from all the centers will be de-identified and managed through a secured code.

### Confidentiality

All information collected in this study will be given code numbers, and no name will be recorded. This cannot be linked to the patients, parents, or a care provider in any way. Identifier will not be used in any publication or reports from this study.

#### Plans for Collection, Laboratory Evaluation, and Storage of Biological Specimens for Genetic or Molecular Analysis in This Trial/Future Use

This trial has no intention to collect the biological samples for a genetic study.

### Statistical Methods for Primary and Secondary Outcomes

Data from this study will be analyzed in GraphPad Prism 9 (GraphPad Software, San Diego, CA, USA). The appropriate descriptive statistics will be used to present the sociodemographic characteristics of study participants. The comparison of categorical outcomes between the arms will be analyzed using the Chi-squared or Fisher's exact tests, as appropriate, and presented as risk differences, risk ratios, or odds ratios and 95% CIs. The values of *p* < 0.05 will be considered statistically significant for all analyses.

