**Methods:**

This RCT will be conducted in two public tertiary teaching hospitals in two of the six geopolitical zones in Nigeria. The sociodemographic and clinical details of all patients admitted to the neonatal wards during the study period will be documented. Study participants will be selected through a multistage sampling technique. Subjects will be randomized and allocated to treatment and control arms having the established baseline measure of social support and religiosity. Ethical approval was obtained from the State Research Ethics Review Committee. A written informed consent will be obtained from the parents/caregivers prior to patient enrolment. The study will be conducted in line with the Declaration of Hesinki 2000. Appropriate statistical tools will be used for data collection and analysis.

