More challenging with DAMA is the ethical issues in neonates as they have the least autonomy to participate in their health decision. The parents/caregivers entrusted with the right of decision-making often fail this vulnerable population. The very sick babies with a risk for residual long-term outcomes, higher risk for mortality, and foreseeable future of being a burden are often thought of dispensing with by the parents/caregivers, and hence there is a request for DAMA. This poses a great challenge to the managing physician on maintaining a balance between the parents/caregivers autonomy against the fiduciary role of the physician (4, 6, 8).

A few observational studies have shown lower incidences of DAMA in faith-based hospitals where spiritual leaders actively participate in patient care (14–20). A holistic approach to patients' care that addresses the spiritual needs, the soul, and the body component of a being in this setting may account for the observed lower incidence of DAMA. However, it may not be sufficient to explain the lower incidence of DAMA with just the involvement of the spiritual leader in care, the literature has suggested that a number of variables can interact to influence decision-making. In this instance, perceived social support of parents/caregivers of newborns as well as their levels of religiosity may significantly influence the decision to engage in DAMA (20–22). Limited randomized control trial (RCT) studies on the effectiveness of faith-based intervention (FBI) are available in the published literature.

This protocol provides a workflow for an open label randomized clinical trial to evaluate the effectiveness of spiritual/FBI intervention on hospital retention of neonates compared with standard of care in tertiary hospitals. It also includes secondary outcomes such as patients' clinical outcome, parents/caregivers' satisfaction with intervention, and their desire to see the intervention established as routine care for newborns in a public tertiary hospital.

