### Trial Design

#### Intervention Assignment

This will be an open label, parallel RCT.

Simple randomization using a randomization table created by a computer software program would be used for randomization.

Allocation sequence would be concealed in sealed opaque envelopes.

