## Methods: Participants, Interventions, and Outcomes

### Study Setting

This study is a multicenter study involving two public tertiary hospitals located in two of the six geopolitical zones/regions in Nigeria (23, 24). The selected tertiary hospital includes University College Hospital Ibadan and The Federal Medical Center Katsina, Katsina state as shown in Figure 2.

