#### Sampling Technique

*In stage I*, the list of tertiary hospitals in Nigeria will form the sample frame for this study. A random number will be allocated to each center. Two institutions will be randomly selected from this list.

*In Stage II*, an allocation sequence for the two arms will be generated using simple randomization from GraphPad Prism version 9. In the selected hospitals, consecutive neonates whose parents/caregivers give an informed consent would be allocated to one of the two arms based on the allocation sequence.

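### The stated between-arm test leaves out hospital and the baseline religiosity and social-support scores; it is valid, but gives up power if these predict DAMA

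*Protocol article*

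**What the plan says.** Under Statistical Methods for Primary and Secondary Outcomes, the protocol article says: "The comparison of categorical outcomes between the arms will be analyzed using the Chi-squared" or Fisher's exact test. It names no stratum and no covariate.

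Allocation is also unstratified. Under Intervention Assignment: "Simple randomization using a randomization table created by a computer software program would be used for randomization". Under Sampling Technique: "an allocation sequence for the two arms will be generated using simple randomization from GraphPad Prism version 9".

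The sites are "two public tertiary hospitals located in two of the six geopolitical zones/regions in Nigeria" (Study Setting). The Abstract says: "Subjects will be randomized and allocated to treatment and control arms having the established baseline measure of social support and religiosity". Table 1 places the research screening tools at enrolment, before allocation.

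Background and Rationale treats place and these scores as possible influences on the outcome: "The DAMA prevalence has been shown to vary depending on geographical areas and the study population", and "perceived social support of parents/caregivers of newborns as well as their levels of religiosity may significantly influence the decision to engage in DAMA".

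Elsewhere, region appears as a subgroup variable (Methods for Additional Analyses). Religiosity and social support appear in a specific objective and a secondary outcome. None of the three enters the stated comparison of arms.

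**The concern.** The protocol names likely predictors of DAMA, has them in hand before allocation, and then compares the arms without them. If hospital or the scores do predict DAMA, the variation they explain stays in the error term, and the trial has less power than its own data could give.

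A chance difference in hospital mix between the arms would also go uncorrected in the reported risk difference, which invites argument about the primary result.

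This matters more because the sample size has little slack. On a two-arm reading, 359 babies give only about 48% power for 50% v 40%.

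**Working it through.** **Inputs from the article.** Total 359; alpha 0.05 (two-sided assumed); DAMA rate 50%; two hospitals; simple randomisation (1:1 assumed). Not given: DAMA rate by hospital, recruitment split, and strength of the scores. These are assumed below and shown as a range.

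**1. The plan's own figure.** The article uses a single-proportion calculator. With an assumed 5% margin, 1.96² × 0.25 / 0.05² = 384.1, so 385. The stated inputs do not give 359. That figure appears with an unstated population of about 5,467, since 384.15 / (1 + 383.15/5,467) = 359.0, or with an unstated margin of about 5.17%. So 359 carries no two-arm effect size. This is a separate issue; 359 is simply taken as N. About 180 per arm has 80% power for roughly 50% v 35.3%, hence the 14.7-point reference effect.

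**2. Crude test.** With 179.5 per arm, the average rate is 0.50 − 0.147/2 = 0.4265.
- Variance: 0.4265 × 0.5735 = 0.2446.
- Null SE: √(0.2446 × 2/179.5) = 0.0522.
- Alternative SE: √((0.25 + 0.2284)/179.5) = 0.0516.
- Power: Φ((0.147 − 1.96 × 0.0522)/0.0516) = Φ(0.87) = 81%.

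**3. Stratifying by hospital.** With two equal sites whose rates differ by g, stratification removes g²/4 from the variance. At 70/30 this is 0.40²/4 = 0.04.
- Variance: 0.2446 − 0.04 = 0.2046.
- Null SE: √(0.2046 × 2/179.5) = 0.0477.
- Alternative SE: √((0.21 + 0.1884)/179.5) = 0.0471.
- Power: Φ((0.147 − 1.96 × 0.0477)/0.0471) = Φ(1.13) = 87%.

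| Assumed control rates | Closed form, crude v stratified | Simulated, crude v CMH |
|---|---|---|
| 50/50 | 81% v 81% | 80% v 80% |
| 60/40 | 81% v 82% | 81% v 82% |
| 65/35 | 81% v 84% | 81% v 84% |
| 70/30 | 81% v 87% | 80% v 87% |

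For a 10-point reduction, simulation gives 48% v 50% at 60/40 and 48% v about 54% at 70/30.

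**4. Adding the scores.** Simulation (2,000 trials per scenario) with two standard-normal scores, each with an assumed log-odds of 0.6 per SD, compared the crude test with logistic regression on arm, hospital and both scores:
- 60/40 sites: 80% v 85%.
- 70/30 sites: 80% v 90%.
- No prognostic factor: 80% v 80%.

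**5. Lower DAMA rates.** Across the same range of assumptions, full adjustment gains 0 to 6 points for 20% v 9.7%, and about 1 to 3 points for 10% v 3%.

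**6. Validity.** Type I error of the crude test was 4.8% to 5.2% with 20,000 trials per scenario. In the smaller runs it was 4% to 7%, which is simulation noise.

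**7. What simple randomisation contributes.** Unequal arm sizes cost about 1/359 = 0.3% of efficiency. Stratifying the allocation while keeping the crude test moved simulated power by no more than about 2 points in either direction, which is noise. Hospital mix differs between arms with SD √(0.25 × 2/179.5) = 5.3 points, so a difference above 10 points occurs in about 6% of trials. At 70/30 such a difference shifts the crude risk difference by 0.10 × 0.40 = 4 points or more.

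**The case against.** The strongest reply is that nothing here is wrong. The crude test holds its error rate, and chance imbalance between hospitals is already counted in that rate. Simple randomisation is valid at this size and is the least predictable scheme for an open-label trial. Covariate adjustment is often left to an analysis plan, and none is shown. Region and the scores do appear elsewhere in the article. Up to a 20-point gap between hospitals, adjusting for hospital alone gains no more than about 2 points of power.

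Most of this stands, and it rules out several stronger readings that a reader might infer:
- **That the two hospitals are very different.** The article says only that they lie in different zones. It gives no DAMA rates by site, and its remark on geography is general.
- **That power is certainly lost.** The article says only that the scores may matter and gives no strength of association.
- **That simple randomisation throws away power.** It costs almost none.
- **That the crude result would be biased or invalid.** It would not.
- **That the trial ignores these factors.** They are absent from the allocation and the between-arm test, but not from the secondary and subgroup aims.

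The point about an unseen analysis plan carries less weight. The article does not leave the method open: it names the test. If an adjusted primary analysis exists elsewhere, this section should be brought into line with it.

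**Conclusion.** The point holds as a matter of efficiency. On the protocol's own premises, the stated test leaves out factors that are measured before allocation and may predict the outcome. The cost runs from nothing (equal hospitals, uninformative scores) to about 7 points of power from hospital alone at 70/30, and about 10 points if both scores are also moderately prognostic. It shrinks when DAMA is uncommon.

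These sizes rest on assumed site rates, equal recruitment at the two sites, assumed score effects and a 14.7-point reduction. The case for changing does not depend on the larger figures, because adjustment loses nothing material when the factors turn out not to matter. It also corrects chance differences in hospital mix.

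**What to change.** In Statistical Methods for Primary and Secondary Outcomes, make the primary comparison a logistic regression of DAMA (or retention) on arm, hospital and the baseline religiosity and social-support scores, with the scores as continuous terms. From that model, report the standardised (marginal) risk difference with its 95% CI. Name CMH by hospital as the minimum adjusted alternative if the model cannot be fitted. Keep the crude chi-squared test as a sensitivity analysis.

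Stratifying the allocation by hospital is optional, and possible only if recruitment has not started. The change to the analysis does not depend on it.

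Cost: a short change of text, slightly more analysis work and possibly software other than the named package. No additional participants or data are needed.
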